### Concomitant care

Participants are allowed to receive other parallel psychotherapeutic treatments for their eating disorder (inpatient, outpatient, self-guided). Other behavioural or supportive care is also allowed, e.g. consultations of general practitioners, nutritional advice, physical activity or dieting programmes. Type of parallel treatment is documented. Concurrent use of psychoactive medications is allowed during the trial with the exception of neuroleptics, benzodiazepines, and opioids as they might interfere with cognitive functioning. Type and dosage of medication is assessed at baseline. If participants with concomitant care are not equally distributed across groups, we will compute sensitivity analyses, e.g. we will rerun our analyses after exclusion of those patients receiving concomitant care, or we will compare the results of those receiving no concomitant care with those receiving concomitant care.

### Participant timeline

The participant timeline is depicted in Fig. 1.

Study duration for each patient comprises 14 weeks. After a baseline assessment (T0, 2 h) including a diagnostic assessment a randomization to either of the three study arms is conducted. Patients get randomized into a) 6 sessions of the food-modified antisaccade training (T1–T6, 20 min each) with feedback, b) 6 sessions of the food- modified antisaccade training (T1-T6, 20 min each) without feedback or c) without treatment during the two weeks. After this two-week span, a post-intervention assessment (T7, 75 min) will be conducted and thereafter a second post-intervention assessment four weeks after training termination (T8, 45 min) and a three-months follow-up assessment focusing on changes in eating disorder symptomatology via telephone (T9, 10 min) will be conducted. In total, the duration of the assessments for the ICT-conditions is around six hours and 10 min across nine appointments. For the waitlist control group, the four appointments take around 4 h and 10 min in total. Details on the investigated outcomes of each time point are presented at Table 1.

**Table 1 Tab1:** Schedule of enrolment, interventions, and assessments within the MIND Binges trial according to SPIRIT

		Baseline	Allocation	Intervention Period	Post-intervention I	Post-intervention II	12-week Follow-Up
**TIMEPOINT**		**T0**		**T1-T6**	**T7**	**T8**	**T9**
ENROLMENT:							
Eligibility screen		X					
Informed consent		X					
Randomization			X				
INTERVENTIONS:							
Inhibitory control training with Feedback							
Inhibitory control training without Feedback							
Waitlist control							
ASSESSMENTS (Instrument):							
Primary outcome:							
BE frequency in the last 4 weeks (EDE)		X				X	X
Secondary outcomes:							
Eating disorder pathology	Eating disorder pathology (EDE)	X				X	
	binge eating frequency in the last 7 days (Process analyses of impulsive behaviours)	X		X (only once per week)	X	X	
	Proportion of (partial) remission of BED (EDE)					X	X
General psycho-pathology	mental comorbidities (SCID-5-CV)	X					
	Depressive symptoms (BDI-II)	X			x	X	
Eating behaviour	Impulsive eating (TFEQ)	X			X	X	
Body Mass Index		X				X	X
Gender (GERAS)		x					
Quality of life (WHO-5)		X			X	X	
Stimulus valence ratings		x			x		
impulsivity	Inhibitory control (Antisaccade task performance)	X		X	X		
	Impulsive behaviours (Process analyses of impulsive behaviours)	X		X (only once per week)	X	x	
	negative urgency (UPPS)	X			x	X	
Motivation (URICA-S)		x			x	x	
Self-Esteem (RSE)		x			x	x	
Treatment expectancy (Self-developed questionnaire)		x					
Self.efficacy	General self-efficacy (IE-4)	X			X	x	
	Food-related efficacy (Self-developed questionnaire)	X			X	x	
Treatment evaluation (Self-developed questionnaire)					x		

*BDI-II *Becks’s Depression Inventory, Version 2; *EDE* Eating Disorder Examination, *GERAS* Gender-Related Attributes, *IE-4* Internal–External locus of control, *RSE* Rosenberg Self-Esteem Scale, *TFEQ* Three-factor eating questionnaire, *UPPS* UPPS impulsive behavior scale, *URICA-S* University of Rhode Island Change Assessment, *WHO-5* WHO (Five)-Well-Being Questionnaire

### Outcomes

Table 1 and Fig. 2 give an overview on assessment points and outcome measures.

**Fig. 2 Fig2:**
[figure not shown]
Participant timeline of the MIND BINGES trial

#### Primary outcome measure

Binge eating frequency in the last four weeks according to the Eating Disorder Examination (EDE) [26] will serve as a primary clinical outcome. EDE is a standardized structured expert interview to assess eating disorder psychopathology. It has shown high inter-rater reliability (Cohens Kappa > 0.80) and internal consistency(Cronbach’s Alpha 0.73 for the subscales; 0.93 for the total score) indicating a good quality of the interview on a superordinate level [26]. EDE includes diagnostic items as well as items related to the four subscales restraint, eating concern, weight concern and shape concern. The diagnostic item 10 is assessing the binge eating frequency in the past four weeks. We compare changes in binge eating episodes at the four weeks follow-up (T8) to baseline (T0) and at the 3-months follow up (T9) to baseline (T0). Binge eating frequency is of high clinical relevance as binge eating resembles the core pathology of eating disorders with regular binge eating [4].

#### Secondary outcome measures

Secondary outcomes will be assessed by validated structured clinical interviews, validated self-report instruments as well as established neuropsychological tasks.

##### Eating disorder pathology

The eating disorder diagnoses will be assessed by the EDE (see primary outcome) [26], which is applied by trained raters. Further, a self-developed protocol assessing binge eating frequency in the last seven days concerning short-term changes will be used [48].The following measures will be assessed additionally to the primary outcome:Eating disorder diagnoses at T0, T8 and T9Severity of eating disorder pathology (general eating disorder pathology, restraint, eating concern, shape concern, weight concern) at T0 and T8.

##### General psychopathology

Comorbid mental disorders are assessed by the *SCID-5-CV* [7]. The *Beck’s Depression Inventory*, Version 2 (BDI-II), is used to assess depressive symptoms [24]. Following measures will be assessed:Number of current and lifetime comorbid mental disorders at T0Severity of depressive symptoms at T0, T7 and T8

##### Gender

Gender will be assessed by the *Gender-Related Attributes* (GERAS) [23]. Following measures will be assessed:Gender-related personality traits (Personality traits, cognitive abilities, interests) at T0

##### Eating behaviour

Eating behaviour will be assessed using the *Three-Factor Eating Questionnaire* (TFEQ) [45]. Following measures will be assessed:Quantification of cognitive restraint of eating, disinhibition and hunger at T0, T7 and T8

##### Body mass index

*Body Mass Index* (BMI) will be obtained by calculating objectively assessed body weight and height at T0 and T8, and self-reported at T9.

##### Quality of life

Quality of life is assessed by the *WHO (Five)-Well-being Questionnaire* (WHO-5) [11]. Following measure will be assessed:Quantification of general mental-well being at T0, T7 and T8

##### Impulsivity and inhibitory control

Impulsivity and inhibitory control will be assessed based on different approaches: On a behavioural level, performance measure of the food-related antisaccade task will be analysed. Further, we will assess different components of impulsivity by self-report measures via the *UPPS Impulsive Behavior Scale* [31] and the *Process analyses of impulsive behaviours* [49]. Following measures will be assessed:Error rate and latency of antisaccades during the food-related antisaccade task at T0, T1 to T6, and T7.Quantification of impulsivity (negative urgency, premeditation, perseverance, sensation seeking) at T0, T7 and T8Frequency of impulsive behaviours at T0, T4, T7 and T8

##### Motivation

Motivation will be assessed by using the *University of Rhode Island Change Assessment* (URICA-S) [8]. Following measures will be assessed:Quantification of Precontemplation, contemplation, change for action and maintenance at T0, T7 and T8

##### Self-esteem

Self-esteem will be assessed by the *Rosenberg Self-Esteem Scale* (RSE) [46]. Following measures will be assessed:

Quantification of global self-esteem at T0, T7 and T8

##### Self-efficacy

General Self-efficacy will be assessed by the *Internal–External locus of control* (IE-4) [33], food-related self-efficacy will be assessed by a novel self-report questionnaire by Krey (2019). Following measures will be assessed:Quantification of internal and external locus of control at T0, T7 and T8Quantification of food-related self-efficacy concerning certain foods, specific situations and general food-related self-efficacy at T0, T7 and T8

##### Treatment expectation and evaluation

Treatment expectation will be assessed by a self-developed self-report evaluation sheet which focusses on app-based training programmes and their expected effectiveness. Following measures will be assessed:Quantification of factors concerning subjective need, motivation for training uptake and overall satisfaction at T0 (treatment expectancy) and T7 (treatment evaluation)Feasibility and acceptability of the treatment will be determined by the percentage of included patients from the eligible patients at T0 and the drop-out rate at T9

##### Valence ratings

Rating of stimulus valence of the food pictures is assessed based on visual analogue scales (−5 to 5). Next to the food images being used in the inhibitory control training which can be subsumized as high-caloric food, stimulus valence of low-caloric food pictures are assessed as well [9]. Following measures will be assessed:Valence („very unpleasant “ to „very pleasant “), appetite („very unappetizing “ to „very appetizing “), wanting („not at all “ to „very much “) and liking („not at all “ to „very much “) at T0 and T7

### Sample size

We base our intended sample size on our randomized-controlled clinical pilot trial [19], where 20 patients per group were sufficient to detect significant effects with a moderate effect size between two groups (treatment vs. active comparator; d ≈ 0.7). With an expected dropout rate of 5% according to Giel et al. [19], we decided to allocate 63 patients in our current trial (n = 21 per study arm).

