### Current study

As the food-modified antisaccade training alone produced strong effects in our previous trial [19], including decreases of binge eating frequency, eating disorder pathology, and antisaccade performance independently from the tDCS condition, we now investigate mechanisms underlying the effects of the food-modified antisaccade training without neuromodulatory support through tDCS. This proof-of-principle trial will investigate the role of feedback in the food-modified antisaccade training to reduce binge eating. In a randomized controlled parallel group design two conditions of the inhibitory control training are implemented: a) with feedback and b) without feedback. Both will be compared to c) no treatment. The superordinate research question of the project is to investigate the role of feedback in the food-modified antisaccade training to reduce regular binge eating behaviours. In more detail, we propose:Noninferiority of the food-related antisaccade training without feedback compared with the original training including feedback in patients with regular binge eating regarding binge eating frequency (primary outcome) and eating disorder pathology, impulsivity, task performance, motivation and self-efficacy (secondary outcomes).Confirmation of clinically relevant effects of the training without feedback against the waitlist control and confirmation of clinically relevant effects of the training with feedback against the waitlist control i.e. superiority in comparison with a group with no treatment regarding primary and secondary outcomes.We will perform regression analyses concerning impact of sociodemographic variables and psychopathology and the treatment outcome depending on the training condition.Subordinate, we are interested in mechanism-driven pathways of effective treatment with ICT in patients with regular binge eating behaviour. Thus, we exploratory investigate the pathways between the primary outcome and secondary outcomes, that also serve as predictors and moderators.

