### Randomization

Randomization will be performed by a staff member of the Department of Psychosomatics and Psychotherapy after finishing the diagnostic assessment at T0. People get randomized in a 1:1:1 ratio to a) inhibitory control training with feedback and post-assessment, b) inhibitory control training without feedback and post-assessment, c) waitlist-control and post-assessment. All arms undergo the four- and twelve-week follow-up.

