### Statistical methods

The primary analysis will use the number of binge eating episodes during the last four weeks in a linear mixed model with baseline adjustment at T8 and T9. In case of non-normally distributed data we want to use generalized linear mixed models as this statistical approach accounts for non-normally distributed data better. To test for noninferiority of the inhibitory control training without feedback compared to the inhibitory control training with feedback, we perform one tailed-tests with an alpha-level of 0.025. Further, we compare if the confidence interval of the inhibitory control training without feedback includes the effect of the inhibitory control training with feedback which resembles the non-inferiority margin [3, 37, 53]. For comparison of inhibitory control training with feedback against the waitlist control and for the comparison of inhibitory control training without feedback against the waitlist control we conduct two-sided tests with an alpha-level of 0.05.

In secondary analyses, a mixed model approach will be used to analyze the secondary outcomes also with baseline adjustment. Effect sizes will be analyzed and reported for primary and secondary outcomes. For binary outcomes, odds ratios and for quantitative outcomes, standardized differences will be reported. Primary parameters will be time vs. treatment interactions at several time points after baseline.

Further, for the regression analyses, a mixed model approach will be used as well. We want to investigate the impact of sociodemographic, comorbid psychopathology (SKID-V, BDI-II), self-efficacy (URICA-S, IE-4, food-related self-efficacy), self-esteem (RSE), treatment expectation (self-developed self-report questionnaire) as predictors on the primary outcome.

Last, for potential mechanisms underlying the inhibitory control training, we will conduct mixed models on the valence ratings of the different food stimuli and its relation to the primary outcome.

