A deeper understanding of underlying mechanisms driving the effectiveness of cognitive trainings is of particular interest. Several potential pathways have been proposed, for example the *devaluation effect* of food stimuli [56], healthy food choices [30] but also eating-disorder-specific traits [10, 16]. Additionally, unspecific traits like self-efficacy, metacognitive self-regulation and self-esteem may also predict positive treatment outcomes [44]. To get a broad view on several variables that might be causal in the treatment outcome we included several variables related and unrelated to the eating disorder to allow for conclusions on effective treatment based on individual predispositions.

Nonetheless, the current trial faces several challenges: In the previous RCT, participants had a 50 percent chance of receiving real transcranial direct current stimulation (tDCS) and still received the inhibitory control training when assigned to the placebo tDCS, which likely enhanced overall acceptability. In contrast, participant engagement in the present trial may be more difficult to ensure, as only the training or a waitlist condition are provided. Moreover, the training alone may not fully address the necessity of multimodal treatment which is demanded by severity of BED and BN [25]. Further, to work out the importance of food-specific ICT, it might make sense to consider another control group instead of a waitlist group: a group receiving a sham training, e.g. ICT with neutral/non-food specific stimuli, could meet these criteria. Last, of study patients might be challenging, in particular to distinguish the effect of the two-weeks ICT intervention from longer-termed concomitant care.

If the training without feedback, i.e. without eye tracking, proves effective in reducing binge eating frequency to a clinically meaningful degree, and ideally achieves outcomes comparable to the training with feedback, this could pave the way for an economically viable digital intervention. Moreover, findings from this trial, including regression analyses, will allow us to examine how sample characteristics influence the effectiveness of inhibitory control training and assess its suitability for potential home-treatment. With the identification of fruitful elements of effective inhibitory control training, the foundation stone is laid for the development of app-based smartphone interventions, which already have a place in basic care of mental disorders [47].

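### The sample size of 20 per arm rests on a significant pilot result for a tDCS contrast, which does not show that this size is sufficient for either of this trial's comparisons

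*Protocol article*

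**What the plan says.** The Sample size section bases the number on the pilot trial, "where 20 patients per group were sufficient to detect significant effects with a moderate effect size between two groups" ("treatment vs. active comparator; d ≈ 0.7"). After an expected 5% dropout, "we decided to allocate 63 patients in our current trial (n = 21 per study arm"). It states no power, no margin and no calculation for this trial's own comparisons.

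Those comparisons are set out under Current study and Statistical methods:
- non-inferiority of training without feedback to training with feedback, listed first and tested one-sided at 0.025;
- each training arm against waitlist, tested two-sided at 0.05.

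The primary model is a mixed model with baseline adjustment at T8 and T9.

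Other sections show what the pilot compared. According to the Discussion, pilot participants had an even chance of real tDCS and "still received the inhibitory control training when assigned to the placebo tDCS". The present trial uses no tDCS (Current study). The pilot had no waitlist arm (Discussion), and its data permit no conclusion about feedback (the Introduction's subsection on feedback).

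**The concern.** The only support offered for the size is that an earlier trial of that size produced a significant result. This raises three problems.

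1. Significance in one trial is an outcome. It does not establish that the design has adequate power.
2. The effect size belongs to a contrast that this trial does not test.
3. The size is reused for a non-inferiority question that needs its own calculation against a margin.

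What is at stake is how the feedback comparison will be read. The Discussion would build an app-based intervention on outcomes comparable to the training with feedback. With wide intervals, an inconclusive result can easily look comparable.

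**Working it through.** **Inputs.** From the protocol: 20 evaluable per arm, d = 0.7, 5% dropout, 1:1:1 allocation, two-sided 0.05 for waitlist comparisons, one-sided 0.025 for non-inferiority. Assumed, because the protocol gives no figure: baseline correlation ρ of 0.3 to 0.7 and non-inferiority margins of 0.35 and 0.65 SD.

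**The plan's own figure.** 20 × 1.05 = 21 per arm, and 3 × 21 = 63. The stated total reproduces. (Dividing instead, 20/0.95 = 21.05, which is immaterial here.) The 20 itself cannot be derived, since no power target is given.

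**What d of about 0.7 measures.** The Sample size section calls it treatment versus active comparator. The Discussion says that placebo-tDCS patients also received the training, so the between-group difference is a tDCS effect. The strong effects credited to the training are a different quantity: Current study reports decreases in binge eating frequency, "eating disorder pathology, and antisaccade performance independently from the tDCS condition". Those are changes over time, with no untreated group.

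**Power for a true d of 0.7.** Noncentral t, 38 df, noncentrality d × √(n/2) = 0.7 × √10 = 2.21, critical value 2.024:
- 20 per arm: 57.8%; 21 per arm: 60.0%.
- 80% power needs 34 per arm.
- The d detectable with 80% power at 20 per arm is 0.91.

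**With baseline adjustment.** The effective d is 0.7/√(1 − ρ²), valid only if 0.7 is not already an adjusted effect:

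| ρ (assumed) | effective d | power, 20 per arm |
|---|---|---|
| 0 | 0.70 | 58% |
| 0.3 | 0.73 | 62% |
| 0.5 | 0.81 | 70% |
| 0.7 | 0.98 | 86% |

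Reaching 80% needs ρ of about 0.64.

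**Precision of a two-arm contrast.** The 95% CI half-width is 2.024 × √(2/20) = 0.64 SD unadjusted. At ρ = 0.5 it is 0.64 × √(1 − 0.25) = 0.55 SD.

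**Non-inferiority power.** True difference 0, one-sided 0.025, 20 per arm, with the margin divided by √(1 − ρ²):

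| margin (assumed) | ρ = 0 | ρ = 0.5 | ρ = 0.7 |
|---|---|---|---|
| 0.35 SD | 19% | 24% | 33% |
| 0.65 SD | 52% | 64% | 80% |

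**How this meets the planned check.** The sentence in Statistical methods that begins "To test for noninferiority of the inhibitory control training without feedback compared to the inhibitory control training with feedback" sets the one-sided test. The next sentence checks whether the no-feedback arm's confidence interval includes the effect in the feedback arm, and names that effect as the margin. If the interval is one arm's unadjusted mean, its half-width is 2.093 × 1/√20 = 0.47 SD (t with 19 df). A no-feedback arm observed to do worse by almost that much would still pass. Fewer patients would widen the interval and make the check easier to meet.

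**The case against.** The strongest reply has five parts.

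- **No power is claimed.** The sufficiency wording reports on the pilot in the past tense. This stands: a reader might infer a wrong power figure or an arithmetic slip, and there is neither. But the sentence is the only justification given for this trial's size, so the inference it invites needs support.
- **The planned model adjusts for baseline, so a flat 58% is not the power of the planned analysis.** This also stands, and the range matters more than its lower end. It is likewise unsafe to infer that the pilot only just reached significance. An observed d of 0.64 is the threshold for an unadjusted t-test at 20 per arm, but the pilot's analysis is not shown.
- **The effect against waitlist may exceed 0.7.** Possible: at d = 0.9 the unadjusted power would be 79%. The documents do not settle it, so power at 0.7 can only be illustrative.
- **The non-inferiority question is not hopeless.** Correct. A reader of the small-margin figures might call it undecidable at this size, but a 0.65 SD margin gives 52-80%. Nor is it exact to say that no margin is named: one is named, without a number.
- **This is a proof-of-principle trial, for which pilot-based sizing is common.** That can justify a small sample. It does not make a tDCS effect relevant to feedback or waitlist contrasts, and the plan still sets formal tests and seeks confirmation of clinically relevant effects.

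**Conclusion.** The concern holds as an unsupported claim of sufficiency, not as an error in a stated power. The borrowed d is a tDCS contrast, and nothing in the protocol sizes the non-inferiority hypothesis. At a true d of 0.7, power lies between about 58% and 86%, depending on a baseline correlation that the protocol does not give and on d not already being adjusted. Non-inferiority power is low for small margins and moderate for larger ones, all of them assumed. The calculations treat the count outcome on an SD scale at a single time point.

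A reader might conclude that the non-inferiority objective has to be abandoned or the trial enlarged. The documents do not force either step. They do require that the expected precision be stated and that wide intervals not be taken as evidence of non-inferiority. This should be fixed, but it does not invalidate the design.

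**What to change.** Keep 63 patients and the non-inferiority objective.

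1. **Sample size section.** Replace the sufficiency sentence with what the trial delivers at 20 evaluable per arm: for d of 0.7, about 58% power unadjusted and about 62%, 70% and 86% at assumed baseline correlations of 0.3, 0.5 and 0.7. Label this illustrative, because the waitlist effect is unknown. Add the 95% CI half-width of a between-arm contrast: about 0.55 SD at correlation 0.5 and 0.64 SD unadjusted. Say that d of about 0.7 came from real versus placebo tDCS.
2. **Statistical methods section.** Report the between-arm feedback difference with its 95% CI. State that neither an interval that merely includes the feedback arm's effect nor a non-significant difference will be read as non-inferiority.

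The first change is rewording, and the stated figures become less favourable. The second withdraws the interval-inclusion check as a basis for claiming non-inferiority. Neither needs more patients, visits or assessments.
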